### Retinal assessment

Annual screening for retinopathy is routinely performed in adolescents with T1D [46]. Anonymised digital copies of the most recent retinal photographs will be collected from each patient at the baseline visit and then during each annual visit until the final assessment. These digital photographs will be used for centralized grading of diabetic retinopathy and, where possible, also for detailed study of the retinal microvasculature.

Stereoscopic fundal photography of seven standard fields is the most sensitive detection methods, which is generally recommended and performed [85]. However, different centers may adopt other validated methods and for the present study, all annually performed retinal photographs with or without mydriasis will be considered. Minimum requirements are a pupil size after dark adaptation of at least 4 mm and two 45-degree photographs taken of each eye, a total of four photographs for retinopathy grading (centered on optic disc and on macula).

Diabetic retinopathy will be graded centrally accordingly to the Early Treatment Diabetic Retinopathy (ETDRS) adaptation of the modified Airlie House classification of diabetic retinopathy [86]. Retinopathy levels for each eye will be classified as follow: level 10: no retinopathy; level 21: at least one microaneurysm or hemorrhage; level 31: microaneurysm plus one or more hemorrhage, exudate, venous bead or loop; level 41: moderately severe non-proliferative retinopathy. The level of retinopathy of the more severely affected eye will be used for assigning the ETDRS grade to a participant.

Digital fundus images should have enough resolution to permit assessment of minor vessel contour. A resolution of 6 microns/pixel or smaller is appropriate. Therefore, where retinal photographs with an adequate resolution and format are available, subclinical retinal microvascular changes, including arteriolar and venular caliber changes, altered vascular fractal dimension, branching and tortuosity, will also be assessed centrally. Retinal vascular caliber and the other vascular aspects will be assessed using a computer program following previously validated protocols [87,88].

### Quality of Life and Health Economics Assessments

An economic evaluation will be conducted to estimate the costs, effects and cost-effectiveness of each IMP and combination therapy in comparison with placebo. It will consist of a within-trial evaluation and a long-term cost-effectiveness analysis using an extrapolation model to estimate costs and outcomes beyond the end of the trial period. Resource use data will be collected on the intervention drugs and consultations and on health care use associated with side effects and complications. Appropriate information will be collected using the CRFs, coupled with a questionnaire *(see additional file *3), administered annually throughout the study period to all 500 randomized and 400 observational subjects, asking about out-of-pocket costs, general practice, out-patients consultations and other expenses and services used. The euroQoI EQ-5D quality of life instrument *(see additional file *4) will also be administered annually; it is widely used and accepted in economic evaluation and permits calculations of utility-based quality adjusted life years. Unit costs will be collected from study centers and from national sources, and will be combined with resource volumes to produce an estimated cost per patient over the study period. Missing data will be dealt with using multiple imputation techniques. Uncertainty will be handled using standard statistical methods and the non-parametric bootstrap.

For the within-trial estimates of cost-effectiveness, effectiveness will be measured using the primary endpoint urinary albumin excretion. For the extrapolated cost-effectiveness, we propose to use the most recent version of the DCCT cost-effectiveness model [89]. This model has been used extensively in economic evaluations of T1D [90] and is available for use by other researchers. The nephropathy module of this model contains a set of nephropathy health states into which the trial's urinary albumin excretion measures can readily be mapped. This will permit long-term cardiovascular morbidity and mortality to be estimated and thence cost per (quality adjusted) life year gained. The model will be adapted to incorporate trial-specific risk factors and population characteristics.

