Clinical trials may need to use surrogate endpoints and non-invasive vascular assessment techniques have demonstrated abnormalities in T1D in early childhood [26,28-32,62]. In particular, cIMT has been shown to be significantly greater in children with T1D than in age-matched controls [26] and not dissimilar to that observed in heterozygote subjects with FH [63]. Other measures of CVD risk and endothelial dysfunction, such as FMD, may precede changes in cIMT within the first decade of T1D in children [26] and other measures such as endothelial pulse amplitude tonometry (EndoPAT) may also distinguish T1D from healthy subjects [64-66]. Arterial stiffness as assessed by pulse wave velocity (PWV) may be an additional marker of CVD, which has been shown to be abnormal in T1D patients as young as 10 years [67]. Statin treatment would be expected to slow the progression or result in regression of cIMT, and a two-year RCT of pravastatin in 214 children with heterozygous FH found active treatment to result in a significant difference in the mean change in cIMT between the two groups [68]. In addition to reducing the risk of CVD, statin therapy may also reduce the risk of nephropathy. Low density lipoprotein (LDL) cholesterol, and small dense LDL in particular, produce proliferative and biosynthetic responses in glomerular cells that occur in the early stages of DN [69]. Mesangial cells can take up both native and modified LDL and respond in vitro by proliferation, production of chemo-attractants for monocytes and macrophages, and alterations to matrix turnover leading to net matrix expansion [70]. Furthermore, diabetes induced mesangial expansion has been shown in animal models to be reduced in a dose dependent manner by statins [71]. Statin treatment is associated with a significant reduction in mean serum creatinine concentration [72] and a recent trial of subjects with diabetes reported a reduction of 11% in patients randomized to atorvastatin for three years whilst patients randomized to standard care showed a 5% increase in creatinine [73]. These findings suggest that statin therapy in T1D may reduce the risk of both DN and CVD. Dyslipidemia has also been implicated in the pathogenesis of retinopathy and consequently statin treatment may be beneficial in limiting this complication [74,75]. Combination therapy with a statin and an ACEI for patients at high risk of development of MA may therefore represent the most effective strategy for reducing future morbidity and mortality from DN and CVD in patients with childhood-onset T1D. Thus both ACEI and Statin therapy could provide cardio-renal protection in high-risk subjects during adolescence and we plan to explore this hypothesis through a randomized controlled trial.

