##### • Sample size determination and power calculations

*Number of Subjects required*

The primary power calculation estimates that 400 subjects will need to be analyzed and we aim to recruit 500 to allow for dropouts and non-compliance.

*Power calculations based on the primary endpoint*

A 30% reduction in ACR is considered a worthwhile and plausible effect size to detect in this population and detection of a 25% reduction would be an advantage. With the 2 × 2 factorial design we plan for follow-up of 100 patients in each of the four arms: Placebo (P), ACEI (A), Statin (S), combination of ACEI and Statin (C). This sample size is informed by the ORPS cohort study (477 participants in the correct age range of recruitment with a mean of 3.5 observations over time) [13]. Within the tertile with the highest ACR standardized for gender, age and duration (defined as standardized ACR > 1.2), the standard deviation (SD) of standardized log to base 10 of ACR was 0.38 (mean 0.28) based on analyzing the final value alone, whereas the SD of the average standardized log ACR repeated over time, defined as area under curve per year, was 0.28 offering a reduction in detectable effect size from 30% to 25%. The primary endpoint is therefore defined as area under curve of log standardized ACR, with standardization for gender, age and duration of disease. The chosen sample size and endpoint provide 93% power to detect a 25% reduction in ACR attributable to the factorial main effect of ACEI (A and A+S arms [n = 200 total] versus P and S arms [n = 200 total]), and of Statin (S and S+A arms [n = 200 total] versus P and P+A [n = 200 total]). Additionally there is 82% power to detect a 30% reduction in ACR, in the following single-arm comparisons: A [n = 100] versus P [n = 100]; S [n = 100] versus P [n = 100]; and S+A [n = 100] versus P [n = 100].

*Power calculations for secondary endpoints*

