The sample size was based on consideration of statistical power to detect a worthwhile and plausible treatment effect. There is adequate power to detect main effects in the factorial design and single-arm comparisons. It is thought unlikely that a substantive interaction will exist between ACEI and Statin as mechanisms differ, and the estimation of the size of any interaction effect is not the primary target of the trial. A factorial design is therefore appropriate on grounds of no substantive interaction [92] and interaction not being the primary target [93].

If an interaction, chance or otherwise, should arise then the trial has the safeguard of the single-arm comparisons. In the event of closure of one arm of the trial there would remain adequate statistical power in the single-arm comparisons. A more detailed statistical analysis plan will be developed from the protocol, incorporating guidelines for factorial trials [92,93].

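### The economic evaluation judges each drug and the combination only against placebo, so as written it can report an acceptable ratio for a combination that one drug alone dominates

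*Protocol article*

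**What the plan says.** In the protocol article, the section on Quality of Life and Health Economics Assessments gives the aim of the economic evaluation: "to estimate the costs, effects and cost-effectiveness of each IMP and combination therapy in comparison with placebo". Within the trial, "effectiveness will be measured using the primary endpoint urinary albumin excretion". A model then extrapolates to long-term costs and quality-adjusted life years, and uncertainty is to be handled partly by bootstrap. No comparison between active regimens is mentioned.

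For efficacy, the primary objective (Study Objectives) is framed against placebo within the 2 × 2 factorial design. The power section for Study 1 gives the factorial main effects and then states: "Additionally there is 82% power to detect a 30% reduction in ACR, in the following single-arm comparisons". Three follow, each with 100 per arm: ACEI versus placebo (A v P), statin versus placebo (S v P) and combination versus placebo (S+A v P).

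The Statistical analysis section tests the interaction first, then estimates main effects and single-arm comparisons. It adds: "If an interaction, chance or otherwise, should arise then the trial has the safeguard of the single-arm comparisons".

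The Background (Previous interventions with ACEI and Statins) suggests that the combination "may therefore represent the most effective strategy for reducing future morbidity and mortality from DN and CVD".

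**The concern.** A patient receives one of four regimens. A decision maker who already has ACEI alone as an option needs to know what adding the statin costs and gains, and likewise for adding ACEI to a statin. A ratio against placebo credits the combination with the effect of its better component and spreads the cost of the weaker one over that effect. A regimen that no one should choose can then carry a presentable ratio, and the same comparator would carry through to the long-term model.

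The efficacy analysis has a narrower version of this problem. If the two drugs interact sub-additively, the open question is whether the second drug adds anything to the first. None of the three single-arm comparisons named in the power section addresses it directly.

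**Working it through.** **Economic comparison.** The article gives no drug costs, so I keep them symbolic. Let cA and cS be the extra costs of ACEI and statin over placebo, e > 0 the effect of ACEI alone over placebo, and g the further effect of adding the statin to ACEI.

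- Combination against placebo: (cA + cS)/(e + g).
- Combination against ACEI alone: cS/g.

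If g = 0, the first ratio is (cA + cS)/e, which is finite. The second comparison is cS more for no gain, so the combination is dominated. Assuming equal costs c, the placebo ratio is 2c/e, only twice the c/e of ACEI alone. With equal costs and 0 < g < e, 2c/(e + g) is always smaller than c/g, because 2g < e + g. The placebo ratio therefore flatters the combination whenever the second drug adds less than the first gives alone. The argument is the same with the drugs exchanged.

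**Single-arm comparisons.** Inputs from the Study 1 power section and the Statistical analysis section: 100 per arm, two-sided 5%, and SD of log10 ACR of 0.28 (area under the curve per year, the primary endpoint) or 0.38 (final value alone).

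- Effect on the log10 scale: d = −log10(1 − reduction), so 25% gives 0.1249 and 30% gives 0.1549.
- SE = SD × √(2/100), so 0.0396 at SD 0.28 and 0.0537 at SD 0.38.
- Power = Φ(d/SE − 1.96).

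The plan's own figure first. For a 30% reduction at SD 0.38, 0.1549/0.0537 = 2.88 and Φ(0.92) = 82%, which reproduces the stated 82%. At SD 0.28, 0.1549/0.0396 = 3.91 and Φ(1.95) = 97%. The stated figure thus matches the final-value SD rather than the SD of the chosen endpoint, so I carry both.

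| Quantity | SD 0.28 | SD 0.38 |
|---|---|---|
| S+A v P significant; first drug 25%, second adds nothing | 88% | 64% |
| S+A v P significant; first drug 30%, second adds nothing | 97% | 82% |
| S+A v A wrongly favours the combination, same cases | 2.5% | 2.5% |
| Power of S+A v A for a further 25% reduction | 88% | 64% |
| Power of S+A v A for a further 10% reduction | 21% | 13% |
| Further reduction detectable with 80% power | 22.5% | 29.3% |

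**When the fallback would be used.** Suppose ACEI alone, statin alone and both each cut ACR by 30%.

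- The interaction contrast is 0.1549 + 0.1549 − 0.1549 = 0.1549, with SE = SD × √(4/100) = 0.056 or 0.076. The ratios 2.77 and 2.04 give power of 79% and 53%.
- In a simulation of 200,000 trials, S+A v P was significant in 97% (SD 0.28) or 82% (SD 0.38) of the trials with a significant interaction.
- The statin main effect averages S v P (0.1549) and S+A v A (0), giving 0.0775 with SE = SD × √(2/200) = 0.028 or 0.038. It too is significant in 79% or 53% of trials, although the statin adds nothing to ACEI.

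**When it would not be needed.** If the statin is inert alone and on top of ACEI, there is no interaction, and its main effect is wrongly favourable in only 2.5% of trials. The main effects then answer the add-on question.

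**The case against.** The strongest reply is that the plan is consistent with itself. Its objective, its power list and its economic comparator are all against placebo. A reader might take the Background remark about the most effective strategy as the trial's hypothesis. It is rationale, and the stated objective does not include superiority of the combination over one drug. That part of the reply stands.

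A reader might also infer that the trial cannot show whether the combination beats a single drug. The documents do not support this. Each factorial main effect contains the add-on contrast: the statin effect averages S v P with S+A v A. The article also argues that a substantive interaction is unlikely. Moreover, the list of three comparisons is a power statement. The Statistical analysis section does not restrict single-arm comparisons to placebo, and it defers detail to an analysis plan that is not shown. The efficacy point is therefore secondary and conditional on an interaction.

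On the economic side, a common placebo reference lets a reader subtract: combination minus ACEI equals (combination minus placebo) minus (ACEI minus placebo), and the bootstrap could supply the uncertainty. So the data can show dominance. Nor does the article set a cost-effectiveness threshold or decision rule, so it would be wrong to say that the combination is formally approved on a placebo ratio. What remains is that the article does more than leave the comparator open: it names placebo as the only one. The subtraction and its uncertainty are not among the stated outputs.

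**Conclusion.** The economic point holds. Followed as written, the evaluation can report an acceptable-looking ratio for a combination that costs more than one drug alone and gains nothing over it. This needs no interaction, only that one drug adds no effect. Its numerical size depends on costs that the article does not give.

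The efficacy point holds in a smaller form. If an interaction is found, the named comparisons do not directly test the second drug's contribution, and S+A v P would be significant in 88–97% (SD 0.28) or 64–82% (SD 0.38) of trials with a 25–30% effect of the first drug and none added by the second. These figures assume 100 analysed per arm, normality on the log10 scale and no gain from covariate adjustment. Neither point is an arithmetic error, and neither undermines the factorial main effects when the effects add.

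**What to change.** In the health economics section, replace the placebo-only comparison with a full incremental analysis of the four regimens: rank them by cost, remove dominated options, report each remaining ratio against the next best, and use the planned bootstrap for uncertainty. Apply the same ordering in the long-term model. This needs no new data and costs little more than wording.

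In the Statistical analysis section, state that if an interaction is found, S+A v A and S+A v S will be estimated with confidence intervals alongside the comparisons with placebo. The cost is two secondary contrasts, with less power than the main effects: 88% or 64% for a further 25% reduction, and only 21% or 13% for a further 10%. For that reason I would not make a claim for the combination conditional on their significance. The estimates and intervals should inform the interpretation.

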### Statistical analysis

Continuous measures will be compared between groups using analysis of covariance, whereas binary outcomes will be compared using logistic regression. These models will involve adjustment for the randomization stratifiers, and for pre-randomization baseline outcomes to improve precision. The primary endpoint was correlated with baseline standardized ACR in the ORPS cohort (r = 0.3) indicating potential improvement in precision of estimated treatment effects. An initial test will be undertaken for exclusion of the factorial interaction of ACEI with Statin, with subsequent estimation of the factorial main effects of ACEI and Statin and single-arm comparisons. Subgroup analyses, for gender and for baseline standardized ACR (using a median split), will be undertaken by adding an interaction between the subgroup variable and factorial main effects followed by estimation within subgroups. Sensitivity analyses, such as for compliance and for raised HbA1c, will involve analysis using the same methods but applied omitting the relevant subjects or the relevant observations within subjects. For the HbA1c sensitivity analysis exclusions will be defined as those observations following the initial occurrence of a change in HbA1c from baseline in excess of 1%. An analysis restricted to the initial two measurements (first year) where short-term compliance is considered greater, will be performed and contrasted with the later period using within-patient analysis. Missing data will be primarily handled by excluding missing observations from analysis and secondly by multiple imputations [91] considering a contrast of both optimistic and pessimistic scenarios for treatment effects. Analyses will be on the primary basis of intention to treat, with as treated and per protocol as secondary. All tests will be two-tailed, and 5% and 1% significance levels will be used for primary and secondary outcomes respectively.

Formal interim analyses have not been incorporated into the design and analysis of the trial because the 3 to 4 year period of follow-up per subject is long relative to the recruitment period, and an interim analysis would detect early improvements without informing maintenance of any effect. The independent DMEC will determine how regularly to review efficacy and safety regularly, based on progressively longer mean treatment durations.

The sample size was based on consideration of statistical power to detect a worthwhile and plausible treatment effect. There is adequate power to detect main effects in the factorial design and single-arm comparisons. It is thought unlikely that a substantive interaction will exist between ACEI and Statin as mechanisms differ, and the estimation of the size of any interaction effect is not the primary target of the trial. A factorial design is therefore appropriate on grounds of no substantive interaction [92] and interaction not being the primary target [93].

If an interaction, chance or otherwise, should arise then the trial has the safeguard of the single-arm comparisons. In the event of closure of one arm of the trial there would remain adequate statistical power in the single-arm comparisons. A more detailed statistical analysis plan will be developed from the protocol, incorporating guidelines for factorial trials [92,93].

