### Methods/Design

#### Design of the RCT

The study is a multicenter randomized trial involving centers in the UK, Australia and Canada *(see additional file *1).

Subjects will be recruited from a pre-screened population of ~3,000 young people with T1D aged 11 to 16 years based on assessment of risk for future CVD and DN. Subjects deemed to be at high risk, based on their albumin excretion rate, will be randomized to a 2 × 2 factorial design contrasting the effects of ACEI, statins, or combination therapy to placebo over a three to four year treatment period. Minimization of variation between study arms in albumin excretion rate, gender, age, diabetes duration, HbA1c, total cholesterol and center location will be undertaken at randomization.

Analysis of the primary endpoint, change in albumin excretion, will be undertaken on an 'intention to treat' basis. Secondary analyses will be undertaken on the basis of 'as treated' allowing for variance in compliance and allowing for subjects who show substantial changes in HbA1c levels. Additional analyses will be undertaken to assess changes in the secondary objectives and to assess the overall effect of the intervention on quality of life and health economics.

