#### Investigational Medical Products (IMPs)

The active drugs (Atorvastatin and Quinapril) will be manufactured by Pfizer, along with appropriate placebos with adherence to Good Manufacturing Practices. Atorvastatin will be provided in a single dose of 10 mg daily for oral administration with an identically labeled placebo (Study drug A). Quinapril will be available at 2 doses: 5 mg and 10 mg with appropriately matched placebo (Study drug Q). Subjects will be started on 5 mg and reviewed after two weeks; if there have been no adverse reactions in this time, the dose will be increased to 10 mg daily, otherwise it will maintained at 5 mg. Any subjects experiencing apparent side effects (postural hypotension or persistent cough) will have the option of changing to the lower dose at any point during the study.

Subjects will be instructed to take two tablets per day; Pharmacists will be instructed to dispense the blinded product according to the schedule and advised that dose of Study drug Q may need to be reduced. All drugs will be given orally as tablets. No subject will be exposed to more than 10 mg of Quinapril or 10 mg of Atorvastatin. Subjects will be treated with the IMPs for a minimum of three years and up to four years depending on age at recruitment.

Both ACEI and Statins are licensed for use in children and adolescents in the UK, Australia and Canada. However the product licenses are related to the treatment of hypertension in non-diabetic subjects and the treatment of hyperlipidaemia in subjects with familial hypercholesterolaemia. To facilitate the use of the drugs in children with T1D an appropriate Clinical Trial Authorization has been obtained from regulatory authorities in the UK, Canada and Australia.

The drugs and placebo will be delivered to Catalent Pharma Solutions, the contracted distribution company that will be responsible for packaging, labeling and distribution of the IMPs to the designated pharmacies at the study sites. Electronic pill bottle monitoring caps supplied by AARDEX (Zug, Switzerland) will be used. These track caps incorporate a micro-electronic circuit, which records each opening and closing in order to track compliance.

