#### Compliance

Subject compliance will be assessed at each 3-monthly study visit, when all unused study drug will be returned and will be recorded in the CRFs by the research nurses. AARDEX electronic pill bottle track caps, which permit checks of the number of times the pill container has been opened between study visits [80,81], will also be used. The track cap data will be available locally through software provided by AARDEX and can be used by the study nurses to encourage compliance and where appropriate introduce interventions to improve compliance. We will also make regular contact with study subjects through newsletters identifying the value of continued involvement in the study protocol.

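### The as-treated and omission analyses chosen for compliance can show an ACR reduction the drug did not cause; a randomisation-based complier estimate from adherence data already collected should lead instead

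*Protocol article*

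**What the plan says.** The hierarchy in Statistical analysis is clear: "Analyses will be on the primary basis of intention to treat, with as treated and per protocol as secondary". The same section has sensitivity analyses for compliance that use the same models, "applied omitting the relevant subjects or the relevant observations within subjects". Design of the RCT gives the as-treated analysis its purpose: "Secondary analyses will be undertaken on the basis of 'as treated' allowing for variance in compliance".

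One further compliance-motivated analysis is planned, which does not select subjects by what they took: "An analysis restricted to the initial two measurements (first year) where short-term compliance is considered greater", contrasted with the later period within patients.

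Adherence is measured in two ways. Investigational Medical Products describes an electronic bottle cap "which records each opening and closing in order to track compliance", and the Compliance section states: "Subject compliance will be assessed at each 3-monthly study visit, when all unused study drug will be returned". Under Withdrawal of study drugs, subjects taken off a study drug are asked to stay in the trial. The article does not define the as-treated grouping or the per-protocol set.

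**The concern.** Whether a subject takes the tablets is decided after randomisation. The Discussion links adolescence with poor glycaemic control and names poor compliance as a difficulty of treatment, and the Background says glycaemic control explains part of the relation between puberty and microalbuminuria. Poor tablet-taking may therefore go with higher ACR for reasons unrelated to the study drug. If so, an analysis that regroups subjects by drug taken mixes the drug effect with the kind of subject who complies.

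At stake is the secondary question of how well the drugs work when taken. The methods the article fixes for that question can produce an apparent benefit from an inert drug, or enlarge a real one. A later analysis plan built from the protocol would inherit them.

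**Working it through.** The plan gives no figure for the effect of non-compliance on these analyses, so there is none to reproduce.

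**Inputs from the article (Sample size determination).** SD of the primary endpoint 0.28 on log10 ACR; 200 v 200 for each factorial main effect. Recruitment of 500 for 400 analysed implies a combined allowance of 1 − 400/500 = 20% for dropout and non-compliance; no separate non-compliance rate is given. The test is two-sided at 5%, the level set for primary outcomes.

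**Assumptions not in the article.** Proportion of non-compliers *c* = 0.1 or 0.2, the same in both groups. Non-compliers have log10 ACR higher by *D* = 0.07 or 0.14 (0.25 or 0.5 SD). The drug has no effect. No covariate adjustment; 0.28 is used as the SD in each group.

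**As treated.** Treated group: the 200(1 − c) compliers on active drug, with mean m. Untreated group: all 200 on placebo, mean m + cD, plus 200c non-compliers on active drug, mean m + D. The untreated mean is m + (cD + cD)/(1 + c), so

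bias = 2cD/(1 + c), and SE = 0.28 × √(1/[200(1 − c)] + 1/[200(1 + c)]).

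For c = 0.2, D = 0.14: bias = 0.056/1.2 = 0.0467; 1 − 10^(−0.0467) = 10.2%; SE = 0.28 × √(1/160 + 1/240) = 0.0286; z = 1.63; chance of |z| > 1.96 is 37%.

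| c | D | bias (log10) | spurious reduction | type I error |
|---|---|---|---|---|
| 0.1 | 0.07 | 0.0127 | 2.9% | 7% |
| 0.1 | 0.14 | 0.0255 | 5.7% | 15% |
| 0.2 | 0.07 | 0.0233 | 5.2% | 13% |
| 0.2 | 0.14 | 0.0467 | 10.2% | 37% |

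A simulation (4,000 runs, 200 v 200, SD 0.28, no drug effect) with heavier non-compliance of 30% in both groups, and non-complier ACR 1.1, 1.25 or 1.5 times that of compliers, gave spurious reductions of about 4%, 10% and 17% and false-positive rates of about 10%, 33% and 78%.

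**Omission of non-compliers.** With equal group means, compliers lie cD below their group mean. The difference between compliers on active drug (A) and on placebo (P) is −(c_A·D_A − c_P·D_P). This is zero when c and D are the same in both groups; the simulation gave 0% and about 5% false positives. It is not zero when they differ:
- 40% non-compliance on active and 20% on placebo, ACR ratio 1.25 (D = 0.097): 0.2 × 0.097 = 0.019, about 4%. Simulated over ratios 1.1, 1.25 and 1.5: about 2%, 4% and 8%, with false-positive rates of 6%, 10% and 18%.
- 30% in both groups, but compliance prognostic only on active drug: about 3%, 6% and 11.5%, with false-positive rates of 6%, 13% and 35%.

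The sign depends on which group has the stronger selection.

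**Complier-average estimate.** This is the intention-to-treat difference divided by the proportion complying on active drug, taking it that placebo subjects do not get the drug. With no drug effect it stayed within 0.5 percentage points of zero in every scenario, with false-positive rates of 4.5–5.6%. With a true 25% reduction in compliers (0.125 on log10), 30% non-compliance and ratio 1.25:
- Intention to treat: 0.7 × 0.125 = 0.0875, about 18%.
- Complier-average: 0.0875/0.7 = 0.125, 25%.
- As treated: 0.125 + 2(0.3)(0.097)/1.3 = 0.170, about 32%.

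Its SE at c = 0.2 is about 0.28 × √(2/200)/0.8 = 0.035, against 0.0286 as treated.

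**The case against.** The hierarchy is conventional, the compliance analyses are secondary or sensitivity analyses, and the article defers detail to a later analysis plan. The mere absence of a complier-average estimate would indeed be no fault. But the article does not leave the choice open: it names as treated as the way to allow for compliance, and that choice can be judged.

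The models adjust for baseline outcome and for the randomisation factors, which include HbA1c, and there is an HbA1c sensitivity analysis. Adjustment may shrink the assumed gap D, and the figures above are before it. It cannot be relied on to remove the gap, because compliance arises after randomisation. The HbA1c analysis itself excludes on a post-randomisation change. The first-year analysis avoids selecting on compliance but does not estimate an effect in those who take the drug.

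Three stronger readings are tempting, and the article does not support them:
- **That the main result is compromised.** Intention to treat is primary and untouched.
- **That omission is biased as as-treated is.** With blinding and matched placebo, omission is unbiased if compliance and its link to prognosis are the same in all arms. The article offers only a possible route to a difference, through side effects such as cough or postural hypotension.
- **That the complier estimate is simply unbiased.** Caps record openings, not ingestion; subjects can stop one drug or have the quinapril dose reduced, so exposure is partial and changes over time; and use of data after withdrawal from the study depends on permission.

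**Conclusion.** The point holds, as a minor one confined to the secondary compliance results. As treated is biased whenever compliance is prognostic. The size, a spurious 3–10% reduction with 7–37% type I error, rests on the assumed 10–20% non-compliance, the assumed 0.07–0.14 gap before adjustment, and the reading that non-compliers on active drug count as untreated. Against the article's 25% target effect this is not negligible. Per-protocol analysis, read as omission, shares omission's condition: it misleads only if compliance, or its relation to ACR, differs by arm. The complier-average estimate keeps its type I error under the null, given outcome data on non-compliers and no effect of allocation except through drug taken.

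**What to change.** In the analysis plan, add a complier-average (instrumental-variable) estimate for each factorial main effect. Use randomised allocation to that drug as instrument, a pre-specified adherence measure for that drug from track caps and returned tablets as exposure, and the covariates of the primary model. Make it the main secondary compliance analysis, and label the as-treated, per-protocol and omission results descriptive.

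The cost is a short addition using data already collected. State its limits beside it. It gives no power beyond intention to treat and has a wider interval. It needs outcomes on non-compliers and no effect of allocation except through drug taken. Its size, though not its validity under the null, depends on the adherence cut-off or dose-response assumption and on bottle openings reflecting ingestion.
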